## Abstract

**Introduction:**

Recent evidence suggests that blue-light phototherapy impacts gut microbiota composition in jaundiced newborns, leading to disturbances closely related to the therapy's side effects. As a result, gut microbiota may serve as a potential intervention target to mitigate these side effects. In this study, we aim to examine the effects of AB-GG (Lactobacillus rhamnosus LGG), Bb-12 (Bifidobacterium animalis Bb-12) and M-16V (Bifidobacterium breve M-16V) and their combination on the intestinal microbiota, metabolomics and phototherapy-related side effects in neonates with jaundice.

**Methods and analysis:**

A total of 100 jaundiced newborns aged two weeks or younger will be included in this randomized, single-blind (the parents knew, but the neonatologists did not know), single-center controlled trial to receive either 10^9^ colony-forming units of AB-GG, Bb-12, M-16V, a combination of the three probiotics with blue-light phototherapy, or blue-light phototherapy alone. The experimental group will be treated with oral probiotics once daily for 30 days, while the control group will receive only blue-light phototherapy. The follow-up duration will last 30 days. The primary outcomes include changes in gut microbiota, metabolomics, and the incidence of phototherapy side effects, assessed after each phototherapy session, as well as on days 10, 20, and 30.

**Ethics and dissemination:**

The study protocol has been approved by the Ethics Committee of our institution. The findings of this trial will be submitted to a peer-reviewed pediatric journal. Its abstracts will be submitted to relevant national and international conferences.

**Clinical Trial Registration:**

http://www.chictr.org.cn/index.aspx, identifer (ChiCTR2000036013).

## Introduction

### Hyperbilirubinaemia and treatments

Hyperbilirubinemia, which manifests as jaundice, is a common benign condition in newborns and one of the leading causes of hospital readmission during the neonatal period (1). It can result from elevated unconjugated or conjugated bilirubin levels. In some infants, jaundice may become severe, with elevated unconjugated bilirubin potentially progressing to acute bilirubin encephalopathy and kernicterus, posing a significant risk of neonatal mortality and long-term neurodevelopmental impairments (2–5). Currently, phototherapy is the most widely used, effective, and safe method to reduce serum bilirubin levels and prevent severe hyperbilirubinemia and bilirubin encephalopathy, and blood exchange therapy may be utilized for patients unresponsive to phototherapy (6, 7).

### Phototherapy and the intestinal microflora

Phototherapy, while effective, is associated with various side effects, such as mother-infant separation, fever, water and electrolyte imbalances, diarrhea, skin damage, bronze baby syndrome, hematological changes, paralytic intestinal obstruction, patent ductus arteriosus, eye damage, and circadian cycle disturbances (8, 9). Research has shown that phototherapy can significantly impact neonatal gut flora and metabolic markers, leading to bacterial flora imbalances that play a crucial role in neonatal jaundice and enterohepatic circulation (10). This disruption may be a significant cause of phototherapy side effects, making gut flora intervention a promising approach to addressing both hyperbilirubinemia and these side effects (11, 12). Previous studies have employed probiotics in treating neonatal hyperbilirubinemia. Probiotics' role in jaundice treatment is mainly related to regulating gut flora, reducing intestinal pH, decreasing β-glucuronidase levels and activity, inhibiting bilirubin enterohepatic circulation, maintaining intestinal motility, promoting bilirubin excretion, and improving feeding tolerance (13–16). Consequently, probiotics represent an alternative therapeutic target for neonatal hyperbilirubinemia, providing a theoretical foundation for using probiotics in the treatment of jaundiced neonates (17, 18).

All three probiotics are among the most extensively studied worldwide and have been certified as safe and effective by the US Food and Drug Administration (FDA) and the European Food Safety Administration (19, 20). Prior research has employed these probiotics in treating various pediatric conditions, such as inflammatory bowel disease, milk protein allergy, and eczema. However, there are limited reports on their use in treating neonatal jaundice, and no systematic clinical research program has been established (21–23). This study aims to investigate the application of these three probiotics in neonatal jaundice treatment and develop a clinical research protocol that may serve as a reference for other neonatal pediatricians.

### Purpose and hypothesis

The objective of this study was to explore whether AB-GG, Bb-12, and M-16V could contribute to neonatal hyperbilirubinemia treatment by regulating gut flora and metabolic imbalances, as well as reducing phototherapy side effects. We hypothesized that children receiving these three probiotics would exhibit a lower incidence of phototherapy side effects. Additionally, we speculated that the experimental group's fecal samples would demonstrate higher diversity and richness in intestinal microbiota compared to the control group. Moreover, we anticipated differences in the dominant bacteria, related metabolites, and metabolic pathways between the experimental and control groups.

## Methods

### Trial design

The study was designed as a randomized, single-blind trial with an allocation ratio of 4:1. (AB-GG combined with phototherapy, Bb-12 combined with phototherapy, M-16V combined with phototherapy, all of the above probiotics combined with phototherapy, or phototherapy alone). The trial was registered at http://www.chictr.org.cn/index.aspx (registration number: ChiCTR2000036013) (24) before enrolling the first participant. Any significant modifications to the trial will be updated on the mentioned website.

### Experiment and subject setup

The trial will be conducted by enrolling newborns admitted to the NICU unit of East Hospital of Shanghai Sixth People's Hospital. As a tertiary hospital, it discharges over 300 newborns annually, including approximately 100 preterm infants and about 150 jaundiced newborns, ensuring a sufficient source of potential participants. All researchers involved have obtained GCP certifications and are either members of the current clinical pediatric team or the pediatric graduate team, guaranteeing the smooth development and execution of basic and clinical trials at any time. The East Hospital of Shanghai Sixth People's Hospital has established a clinical research center and obtained clinical trial qualifications. Recruitment started in June 2021 and will be completed over the following there years.

### Eligibility criteria

(1)Inclusion criteria: (1) Jaundice index: According to the American Academy of Pediatrics phototherapy guidelines, the jaundice index reaches the phototherapy threshold; (2) age ≤2 weeks; (3) Term infants with 37 weeks ≤ gestational age < 42 weeks and 2,500 g ≤ birth weight < 4,000 g; (4) No prior use of antibiotics or ecological agents before specimen collection; (5) Healthy mothers during pregnancy, with no history of special drug use, and no intake of antibiotics or microecological agents before, during, or after childbirth; (6) Enrolled infants were exclusively breastfed, exclusively formula-fed, or mixed-fed before admission; (7) All enrolled infants had neonatal pathological jaundice as defined by “Practical Neonatology” and required hospital admission solely for phototherapy; (8) Informed consent provided voluntarily.(2)Exclusion criteria: (1) Gestational age <37 weeks or ≥42 weeks; (2) bilirubin levels reaching the exchange blood transfusion standard or elevated direct bilirubin; (3) complications with pneumonia, septicemia, or other diseases; (4) patients with severe immunodeficiency diseases; (5) those with inherited metabolic diseases; (6) congenital biliary malformations or other organ malformations; (7) drug allergies; (8) situations that may warrant exclusion as determined by the researcher, such as a guardian with mental illness or frequent changes in living or working environments, which may result in loss of follow-up.(3)Elimination criteria: (1) Those refusing the use of their newborn information and their stools and blood; (2) During the treatment process, other drugs might be needed to be added because of other diseases, such as the use of antibiotics and micro-ecological agents.(4)Criteria for withdrawal from the study: (1) participants who suddenly refuse stool and blood collection and request to withdraw from the study; (2) severe gastrointestinal symptoms, such as intense vomiting, diarrhea, or abdominal distension, and other adverse events that significantly affect the treatment process during the probiotics intervention; (3) neonates requiring exchange blood transfusion due to the continued worsening of jaundice after active phototherapy; (4) neonates lost to follow-up, unreachable, or unable to return to the study center for visits.

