(1)Definition of adverse events: In this clinical trial, adverse events are defined as severe vomiting, diarrhea, disruption of normal eating habits, or significant necrotizing enterocolitis occurring during the use of probiotics. Additionally, an adverse event is defined as a severe increase in jaundice value that reaches the index for exchange transfusion.(2)Diagnostic criteria of adverse events: (1) Severe vomiting:vomit 5 or more times per day for 2 or more days; (2) Diarrhea 8 or more times per day for 2 or more days; (3) Necrotizing enterocolitis:Neonatal necrotizing enterocolitis is diagnosed according to the Clinical guidelines for the diagnosis and treatment of neonatal necrotizing enterocolitis (2020); (4) According to the Clinical Practice Guideline Revision: Management of Hyperbilirubinemia in the Newborn Infant 35 or More Weeks of Gestation, exchange transfusion criteria have been met.(3)Degree of adverse events: (1) Mild: Neonates can tolerate the event, which does not affect treatment, does not require special treatment, and has no impact on the neonates' health. (2) Moderate: Neonates find the event unbearable, affecting the treatment and having a direct impact on their health. (3) Severe: The event endangers the neonate's life, potentially causing death or disability, and requires immediate emergency treatment.(4)Possibility of adverse events: Although every bacterium in the probiotic combination used in this study is approved by the National Ministry of Health as safe and reliable, adverse events cannot be completely ruled out. However, the probability of adverse events is expected to be low(5)Treatment of adverse events, follow-up methods, and time: In case of adverse events, the incident will be promptly reported, and the clinical trial for the affected neonate will be terminated in a timely manner to prioritize their safety. The patient's stool and gastrointestinal symptoms will be monitored daily, and plain abdominal radiographs will be performed as needed. For patients with severe jaundice requiring exchange transfusion, exchange transfusion therapy will be immediately initiated, as well as monitoring jaundice dynamically and conducting brain MRI and brainstem auditory evoked potential assessments. Post-discharge follow-up will be conducted, selecting various follow-up methods based on the situation. If a neonate with jaundice experiences adverse events after taking probiotics or if such events are suspected to be related to the probiotic administration, strict records should be maintained, the adverse event form should be completed, and the main responsible personnel and the Clinical Research Center of the East Hospital of Shanghai Sixth People's Hospital will be informed within 24 h according to the established process. The ethics committee will decide whether to halt the trial immediately.(6)Risk prevention of adverse events: All adverse events occurring during treatment will be graded according to severity and documented in detail using a CRF (Case Report Form). The potential relationship between adverse events and probiotics will be analyzed. If severe adverse reactions occur, the trial should be stopped immediately. Serious adverse events must be reported in strict accordance with the relevant provisions of GCP (Good Clinical Practice). The group will not receive any drugs or additional probiotics in their milk.

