
### Study procedure

Figure 1 illustrates the details of the research procedure. Parents will continue to receive information about the study for 30 days after enrollment when the newborn has confirmed that neonatal hyperbilirubinemia has met the criteria for phototherapy for the appropriate age, including during their regular follow-up visits to the hyperbilirubinemia clinic. Pediatricians participating in the study will sign written informed consent with parents. Subjects will be randomly assigned to receive AB-GG combined with phototherapy, Bb-12 combined with phototherapy, M-16V combined with phototherapy, all of the above probiotics combined with phototherapy, or phototherapy alone, following the method of a digital randomization list. The probiotic dose is 10^9^ colony-forming units (5 drops) administered orally once daily for 1 month. All subjects will be followed up for 1 month after the start of the intervention. Data and specimen collection on days 10, 20, and 30 will be completed during the outpatient follow-up for hyperbilirubinemia.

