The investigator will re-check the inclusion/exclusion criteria on the first day, perform patient management, conduct detailed physical and serologic examinations prior to phototherapy, and record the adverse events described in Table 1. They will collect stool and blood samples from the subjects. Subjects will receive the first 12 h of phototherapy and the assigned probiotics before phototherapy. After 12 h of phototherapy, researchers will observe phototherapy-related side effects (including body temperature, rash, stool frequency and shape, etc.), record information, collect stool samples, and measure TCB. On the next day, after 6–8 h of rest, the infant will receive a second 12 h phototherapy session while the assigned probiotics are orally administered, and the researchers will again assess and collect fecal samples. The same process will be followed for the third day, and if necessary, subjects may continue with the fourth and fifth 12 h phototherapy sessions, with at least 6 h of rest after each phototherapy session. Stool collection will still be required after each phototherapy session. Subjects will not require further phototherapy and will be discharged once they meet the discharge criteria.

Upon meeting the discharge criteria, the investigator will perform subject management, a detailed physical examination, serological testing, and evaluation of adverse events prior to discharge. Study follow-up on days 10, 20, and 30 will be completed at the outpatient follow-up for hyperbilirubinemia, during which stool and related data will be collected. Infants in the experimental group will continue to receive their assigned oral probiotics during hospitalization after enrollment and during outpatient follow-up for one month.

Stool samples weighing 500 mg and blood samples measuring 0.5 microliters were collected from each subject. The stool samples will be stored at −80°C after freezing, while the blood samples will be tested immediately. There would be no restrictions on the feeding patterns of both the experimental and control groups during the study. Parents are allowed to freely choose between breastfeeding, artificial feeding, and mixed feeding.

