### Endpoints

(1)Primary endpoint: significant reduction in the incidence of clinical side effects (i.e., diarrhea, rash, fever, vomiting, convulsions, feeding intolerance, etc.).(2)Secondary endpoints: after the addition of probiotics, the intestinal flora will be maintained in a stable state after phototherapy, and the changes in metabolic indicators; changes in jaundice (i.e., serum bilirubin, bile acid and transcutaneous bilirubin data), feeding status, changes in urine volume and weight, and vital signs during phototherapy

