### Blinding

The trial is designed to be single-blind. All neonatologists wouldn't be aware of the group assignments throughout the study, while the parents would be aware of their group assignment to the experimental or control groups.

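### The withdrawal rule removes reachable infants who cannot return to the centre, so day 10 to 30 side-effect and safety data that parents could report are lost

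*Protocol article*

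**What the plan says.** Protocol article, Eligibility criteria, part (4) (withdrawal from the study), item (4), lists "neonates lost to follow-up, unreachable, or unable to return to the study center for visits". The three grounds are joined by 'or', so inability to return suffices even when the family can be reached.

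The Endpoints section defines the primary endpoint as "significant reduction in the incidence of clinical side effects", with diarrhea, rash, fever, vomiting, convulsions and feeding intolerance as examples. The Abstract gives the timing of the primary outcomes: "assessed after each phototherapy session, as well as on days 10, 20, and 30".

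Two routes of collection are described under Study procedure. In hospital: "After 12 h of phototherapy, researchers will observe phototherapy-related side effects". After discharge: "Data and specimen collection on days 10, 20, and 30 will be completed during the outpatient follow-up for hyperbilirubinemia". No remote route is given for the scheduled day 10, 20 and 30 data.

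Flexible contact appears in one place, the paragraph on treatment and follow-up of adverse events under Interventions: "Post-discharge follow-up will be conducted, selecting various follow-up methods based on the situation".

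Under Blinding, "the parents would be aware of their group assignment to the experimental or control groups".

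**The concern.** The criterion treats an infant who cannot be found and an infant whose parents answer the telephone but cannot travel in the same way: both leave the study. For the second infant the loss is avoidable. Most listed side effects can be seen by parents, and the adverse-event definitions for severe vomiting and diarrhea are daily counts over two or more days, which a parent can give by telephone.

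At stake are the primary endpoint and safety between discharge and day 30, while the probiotic is still being given. Because parents know the arm and control families have no product to continue, attendance could depend on arm, on symptoms, or on both. An analysis plan can say how missing data are handled, but it cannot recover data that the conduct rule stopped being collected.

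**Working it through.** **1. What the rule removes**

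| Data | When and how collected | Effect of the rule on a reachable infant who cannot attend |
|---|---|---|
| Side effects after each session | In hospital, before discharge | Already recorded; the document does not say they are discarded |
| Side effects on days 10, 20, 30 | Outpatient visit | Collection ends, although most items are parent-reportable |
| New adverse events to day 30 | Outpatient visit | Collection ends, although parents could report them |
| Stool, transcutaneous bilirubin | Outpatient visit | Missing for an unattended visit under any rule |

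The avoidable loss is the second and third rows. It also includes stool and bilirubin at any later visit that the family could have attended had the infant stayed in the study.

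**2. The plan's sample size and its reserve**

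Inputs (Sample size section): 47% versus 10%, type I error 0.05, power 0.80. The two-proportion formula with unpooled variance, two-sided, no margin and no allowance for loss, gives

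n = (1.960 + 0.842)² × (0.47 × 0.53 + 0.10 × 0.90) / 0.37² = 7.851 × 0.3391 / 0.1369 = 19.4, so 20 per group.

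This reproduces the plan's 20. The Randomization section enrols exactly 20 per group, so there is no stated reserve. Keeping 20 evaluable per group would need 20/0.95 = 21.1, so 22, at 5% loss; 20/0.90 = 22.2, so 23, at 10%; and 20/0.80 = 25 at 20%. These loss rates are assumptions.

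**3. Illustrations that need a further assumption**

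Everything in this step assumes that withdrawn infants are left out of the incidence altogether, in-hospital data included. The document does not say so.

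*Power.* Exact enumeration of the two-sided 0.05 Pearson test for 47% versus 10%, with equal assumed loss in both arms:

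| Evaluable per arm | Assumed loss | Power |
|---|---|---|
| 20 | none | 78.4% |
| 18 | 10% | 72.4% |
| 16 | 20% | 70.4% |
| 14 | 30% | 62.5% |

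*Distortion within one arm.* Let r1 and r0 be the return rates of infants with and without a side effect. The observed rate is 0.47 r1 / (0.47 r1 + 0.53 r0).

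- r1 = 0.90, r0 = 0.70: 0.423 / (0.423 + 0.371) = 53%
- r1 = 0.95, r0 = 0.80: 0.4465 / (0.4465 + 0.424) = 51%
- r1 = 0.70, r0 = 0.90: 0.329 / (0.329 + 0.477) = 41%

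*Distortion of the comparison.* Suppose there is no true effect (47% in both arms) and the control arm has no loss related to symptoms. If a fraction L of a probiotic arm is lost and a share e of those lost had a side effect, the observed rate is (0.47 − L × e) / (1 − L).

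- L = 0.20, e = 0.8: 0.31 / 0.80 = 38.8%, a spurious reduction of about 8 points
- L = 0.10, e = 0.8: 0.39 / 0.90 = 43.3%, about 4 points

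If the in-hospital data are kept, none of the figures in this step apply. The loss is then confined to days 10 to 30, and the document gives no event rate or attendance rate from which to size it.

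**The case against.** **A single missed visit.** A reader might infer that one missed day 10 visit ends participation. The text does not support that: it speaks of inability to return for visits, in the plural, and can be read as an infant who can no longer attend at all. This objection stands, and the point is limited to reachable families who cannot attend.

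**Loss of in-hospital data.** A reader might also infer that withdrawn infants and their in-hospital data drop out of the primary comparison. The document does not say this, and analysis sets may be defined in a plan that is not shown. This stands too. The power and bias figures are illustrations under an assumed exclusion. Moreover, the planned 47% refers to digestive side effects caused by phototherapy, so applying post-discharge return rates to all of it presumes that the in-hospital records are set aside.

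**Differential loss.** The post-discharge visits belong to the regular hyperbilirubinemia follow-up that infants in every arm attend. Loss that differs by arm is plausible with open assignment but is not shown.

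**Existing safeguards.** Exclusion criterion (8) lets the researcher screen out families likely to be lost, and the Monitoring section has adverse events followed until resolved or stable. These reduce the problem, the second for events already known. Neither captures a new event in an infant already withdrawn for not attending.

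**Limited gain.** Remote contact yields no stool or bilirubin, and the symptom reports come from unblinded parents. That is true, but an imperfect symptom report is more use than none for the primary endpoint and safety.

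**Conclusion.** The point holds in a limited form. The printed criterion withdraws reachable infants because they cannot travel, and so gives up day 10 to 30 side-effect and adverse-event data that could be had by telephone. This rests on the wording of the criterion, the Abstract's timing of the primary outcomes and the clinic-only collection of later data, not on any assumption about analysis.

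The size is not computable: the document states no attendance rate, no loss rate and no post-discharge event rate. With 20 per arm and no stated reserve, small numbers matter; one infant is 5% of an arm. Dependence of loss on arm or symptoms is a risk, not a demonstrated bias. The change should be made because it protects primary and safety data at little cost; the document does not show the trial's power or comparison to be already compromised.

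**What to change.** Amend withdrawal item (4) and the related follow-up text:

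- Restrict the item to infants who cannot be contacted by any means. Withdrawal at the parents' request remains a separate ground.
- For a reachable infant who cannot attend, record that visit as missing, keep the infant in the study, and allow attendance at later visits.
- Collect the listed side effects and adverse events for that visit by telephone or other remote contact, using the same questions in all five arms. This extends to scheduled follow-up the flexible methods already foreseen for adverse events, and reconciles the two sections.
- State that side-effect data already collected, including all in-hospital data, stay in the primary comparison.
- Record the reason for each unattended visit by arm, so that any imbalance can be seen.

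Whether product is continued is a separate clinical decision and is not addressed here.

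The cost is one amended clause and some telephone calls. The downside is that remote parent reports are less exact than a clinic examination and come from parents who know the arm, so remote and clinic reports should be distinguishable in the data. Stool and transcutaneous bilirubin for the unattended visit remain missing.
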